## Abstract

**Background:**

Vulvodynia is defined as vulvar pain for at least 3 months without a clear cause. To the best of our knowledge, there are no trials investigating the effects of internet treatment using CBT (Cognitive behavioural therapy) treatment with Acceptance and Commitment Therapy (ACT) components for women with vulvodynia. The aim of this study is to examine the effects of such a guided internet-based intervention on provoked vulvar pain during the waiting period before clinical treatment.

**Methods:**

We will randomise 52 patients to either guided internet-based intervention with CBT with (ACT) components or no intervention during the waiting period for treatment as usual. Online assessments are conducted at baseline, posttreatment, and at follow-up after 9 months. The primary outcome measure is provoked vulvar pain. Secondary outcomes are depression, anxiety, sexual function, and quality of life. Linear-mixed effect models will be used to assess the effect of the internet-based intervention on vulvar pain, pain acceptance, depression, anxiety, sexual function, and quality of life over time, by applying the intention-to-treat approach. Continuous data will be analysed with general linear models using intention-to-treat and also per protocol approaches to assess the effects of the intervention at different time points. Ordinal and binary data will be analysed with Mann Whitney's test, Fischer's exact test and multivariate logistic regression, respectively.

**Discussion:**

As a randomised controlled trial with short- and long-term follow-up points, the EMBLA study intends to provide a novel and better understanding regarding the treatment of vulvodynia and the role of internet-based treatment as a complement to standard care for women suffering from vulvodynia. The effects of vulvodynia on pain, sexual function, quality of life, depression, and anxiety are investigated. The study's results are expected to be of value in the planning of clinical care in the medical area. High dropout rates and technical difficulties associated with using the platform are common in similar studies.

**Trial registration number:**

NCT02809612

## Introduction

1

Vulvodynia is defined as vulvar pain lasting for at least 3 months without a clear cause (Bornstein et al., 2016). In provoked vulvodynia, pain is experienced upon mechanical stimuli such as the use of a tampon or vaginal intercourse (Bohm-Starke, 2010; Bornstein et al., 2016; Bornstein et al., 2019; Henzell and Berzins, 2015). The prevalence of vulvodynia varies between studies, but it has been estimated at 10–28%, affecting mostly women between 20 and 30 years (Bohm-Starke, 2010; Reed et al., 2012; Vieira-Baptista et al., 2014; Pukall et al., 2016; Reed et al., 2012; Sadownik, 2014). The aetiology is not clear, but a combination of psychosocial and pathophysiological mechanisms is believed to contribute to the onset (Bergeron et al., 2020; Bornstein et al., 2016; Faye and Piraccini, 2020). Regarding treatment, a multidisciplinary approach is recommended, and pelvic floor physiotherapy and cognitive behavioural therapy (CBT) are considered first line treatment (Bergeron et al., 2020; De Andres et al., 2016; Rosen and Dawson, 2019; Sadownik, 2014, van der Meijden et al., 2017).

Some trials have investigated the effects of CBT for patients with vulvodynia and found positive results on pain, sexual function, psychological adjustment, and treatment satisfaction for patients with vulvodynia (Bergeron et al., 2001; Bergeron et al., 2016; Goldfinger et al., 2016; Lindstrom and Kvist, 2015; Masheb et al., 2009). There are also promising results regarding CBT intervention delivered via the internet for women with sexual dysfunction, including genital pain (Jones and McCabe, 2011). Further, in two trials regarding mindfulness cognitive therapy, also called third wave cognitive behavioural therapy, an effect, similar to CBT, on pain and sexual function is reported (Brotto et al., 2015; Guillet et al., 2019).

Whilst some research has been made on the effects of CBT for vulvodynia, knowledge about the effects of Acceptance and Commitment Therapy (ACT), also part of third wave cognitive behavioural therapy, on provoked vulvodynia is lacking. ACT offers an alternative to traditional attempts to control unwanted psychological experiences by developing acceptances skills to regulate behaviour (Zhang et al., 2017). Instead of trying to control form and frequency of thoughts and feelings, the focus of ACT is on improving functioning and decreasing interference of pain by altering the function, i.e. by increasing psychological flexibility, which can be defined as the ability to act in accordance with one's values and goals despite pain (Feliu-Soler et al., 2018; Hayes and Lillis, 2013; Hayes et al., 1999; Hayes et al., 2006; McCracken and Vowles, 2014; Trompetter et al., 2015a, Trompetter et al., 2015b; Vowles and McCracken, 2008; Vowles et al., 2014). There are six core processes in ACT: 1) acceptance (embrace private events without attempts to change their frequency or form), 2) cognitive defusion (attempt to alter undesirable functions of thoughts without trying to alter their frequency or form), 3) being present (non-judgmental contact with events as they occur), 4) self as context (awareness of one's own experiences without attachment to them), 5) values (choose life directions), and 6) committed action (act according to one's values) (Hayes et al., 2006).

Previous research indicates that ACT is more effective than no treatment for chronic pain (Hann and McCracken, 2014; Hughes et al., 2017; Yu and McCracken, 2016). There are also promising results for ACT delivered via the internet (Buhrman et al., 2013; Buhrman et al., 2015; Carlbring et al., 2018; Lin et al., 2017; Trompetter et al., 2015a, Trompetter et al., 2015b), but knowledge about if it is suitable for vulvar pain is lacking. Cognitive behavioural factors are associated with experience of pain and sexual functioning, suggesting that addressing emotional and sexual cognitive factors is important in vulvodynia management (Chisari and Chilcot, 2017; Chisari et al., 2021).

Vulvodynia has a negative impact in women's well-being and psychosexual function (van der Meijden et al., 2017), and the care available may vary depending on local resources (Bergeron et al., 2020). Internet interventions improve accessibility of health care services (Andersson, 2018; Andersson et al., 2019; Feliu-Soler et al., 2018), but its effects have not yet been investigated in a population with vulvodynia. To fill the knowledge gap regarding internet interventions for vulvodynia, the EMBLA study was developed to investigate the effects of guided internet treatment using ACT-principles for women with vulvodynia during the waiting period before clinical treatment.

### Primary objectives

1.1

The aim of this study is to examine the effects of a guided internet intervention on provoked vulvar pain, compared with no intervention during the waiting period before clinical treatment compared with the waiting period in conjunction with treatment.

### Secondary objectives

1.2

The secondary objectives are to examine the effects of guided internet intervention on depression, anxiety, sexual function, and quality of life.

## Methods

2

### Study design

2.1

The EMBLA study is a multi-centre randomised trial initiated by the Department of Obstetrics and Gynaecology at Uppsala University Hospital, Uppsala, Sweden. The trial will be reported in accordance with the CONSORT guidelines (Schulz et al., 2010).

### Eligibility criteria

2.2

Inclusion criteria include:➢Symptoms of vulvodynia for at least 6 months, and confirmation of the medical diagnosis at the gynaecologist's appointment after study recruitment from waiting lists for clinical treatment, or by the woman herself following study recruitment through social media.➢Access to a computer with internet connection.➢Age of ≥18 years.➢A Swedish personal identification number for access to the treatment platform.

Exclusion criteria include:➢Unclear diagnosis at the screening interview.➢Ongoing examination/treatment related to vulvodynia.➢Lack of fluency in Swedish, since the treatment is delivered in Swedish.➢Severe, acute, or untreated mental illness or substance abuse.

### Study population and recruitment

2.3

Women have been assessed for eligibility since 2016 and the aim is to complete recruitment during 2020. Patients with vulvodynia are recruited from waiting lists for clinical treatment at gynaecological clinics in four counties in Sweden (Falun, Gävle, Uppsala, and Örebro), and through advertisements in social media. The women then receive detailed information about the study over the telephone by the research team. The same information in written form is sent by regular post. Participants are included only after a telephone screening interview performed by one of the researchers, and after they return a signed consent form. A structured questionnaire for diagnostics and evaluation of symptoms developed by the Swedish Working and Reference group for Vulva Diseases, (SFOG, 2013), and structured questions about psychological symptoms, are used for suitability screening in the study. The screening interview is usually scheduled after, but may also occur before, a gynaecologist's appointment. Participants recruited via social media are included in the study only if they can confirm a previous medical diagnosis of vulvodynia and had no ongoing treatment for vulvodynia when they enrol the study. After inclusion, patients fill out the baseline questionnaire and are then randomised to the intervention or control groups.

### Randomisation

2.4

Participants provide informed consent at T0 and are thereafter informed about which group they are allocated to, either the internet treatment group or the control (no treatment) group. Randomisation and allocation are performed using simple randomisation. The randomisation list is created using an automated, web-based randomisation program (https://www.graphpad.com/quickcalcs/randomize2/).

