### Sample size calculation

2.7

Sample size calculation was based previous clinical experience based on self-reported vulvar pain using a Visual analogue scale, which is a Likert scale between 0 and 10, where 0 represents no pain and 10 represents the worst possible pain; this is regularly assessed with questions on pain at intercourse or tampon insertion, which are posed during the first appointment with gynaecologists at Uppsala University Hospital. A minimum of 26 patients in each group at each time point is estimated to give 80% power for ascertain a difference between the groups at a significance level of *p* < 0.05 for a minimum clinically significant improvement of at least 1.2 units in the Visual analogue scale for vulvar pain, as described above, with an estimated 20% drop-out rate.

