### Statistical analysis plan

2.9

Linear mixed effect models will be used to assess the effect of the internet-based treatment on vulvar pain, pain acceptance, depression, anxiety, sexual function, and quality of life over time, by applying the intention-to-treat approach. Variables that vary significantly between groups at baseline will further be adjusted for in the model. Linear mixed modelling is a frequently recommended method for its abilities to handle missing data and correlated observations in repeated-measures data (Gueorguieva and Krystal, 2004; Yoo, 2010). The best-fitted model to the data consists of an unstructured covariance matrix using the restricted maximum likelihood (REML) estimation procedure. Baseline, posttreatment and follow-up measures will be used as repeated measures and intervention/control group will be used as fixed factors.

As significant drop-out is common in internet-based interventions, further analyses will be performed. Continuous data will be analysed with general linear models using besides intention-to-treat also per protocol approaches to assess the effects of the intervention on vulvar pain, depression, anxiety, sexual function, and quality of life at different time points (post-treatment and follow-up). Last observation carried forward (LOCF) will be used for the intention-to-treat analysis. Complementary analysis using worst case imputation and analysis using a per-protocol approach without imputation will also be carried out. Effect size will be calculated with Cohen's d. *P* values less than 0.05 will be considered statistically significant. Ordinal (impact of pain on sexual function) and binary data (willingness to perform tampon test and attempt at vaginal intercourse) will be analysed with Mann Whitney's test, Fischer's exact test and multivariate logistic regression, respectively, to assess differences between groups at posttreatment and follow-up. The binary data are referring to secondary outcomes and will be analysed using a per protocol approach only. Descriptive statistics at baseline and the corresponding changes during follow-up both will be provided in tables and graphically. All analyses will be completed using the IBM SPSS statistical package.

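### Recruitment stream is neither balanced by the simple randomisation nor prespecified in the model, and the rule of adjusting only for significant baseline differences would usually miss a chance imbalance in it.

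*Protocol article*

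**What the plan says.** The Randomisation section states "Randomisation and allocation are performed using simple randomisation" and "The randomisation list is created using an automated, web-based randomisation program". It names no blocks and no strata. The Abstract gives the total: "We will randomise 52 patients to either guided internet-based intervention". The Sample size calculation section sets the target: "A minimum of 26 patients in each group at each time point is estimated to give 80% power".

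The Study population and recruitment section describes two routes into the trial. One is waiting lists for clinical treatment at gynaecological clinics in four counties. The other is advertising: "Participants recruited via social media are included in the study only if they can confirm a previous medical diagnosis of vulvodynia", with the further condition that no vulvodynia treatment is ongoing at enrolment. A place on a waiting list is not among the conditions for this second group.

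The Statistical analysis plan section adjusts the mixed model for variables that differ significantly between the groups at baseline. Recruitment stream is not named as a covariate. Assessments are at baseline (T0), 6 weeks (T1) and 9 months (T2). Elsewhere the article plans to use medical records to account for parallel clinical treatment during the intervention period and to count vulvodynia-related visits.

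**The concern.** Women on a waiting list are due for clinical treatment, and some will probably have begun it by 9 months. Women who answered an advertisement need only a past diagnosis and no current treatment. Stream is therefore a plausible predictor of treatment received by T2, and it is known before allocation. Simple randomisation leaves the stream mix of each arm to chance, which matters more with 52 women than it would in a large trial.

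The analysis rule is the only stated safeguard, and it depends on a significance test at baseline. With about 26 women per arm that test has little power, so an imbalance large enough to matter would usually go unadjusted. What is at stake is the precision and reading of the T2 comparison. Nothing comparable is shown for T1, at 6 weeks.

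**Working it through.** **Inputs.** Total 52, target 26 per group, 80% power, alpha 0.05 and difference 1.2 units are in the article. Not in the article, so assumed: 1:1 allocation probability (implied by 52 = 2 × 26), a two-sided test, and a smaller stream of m = 5 to 26 women.

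**The plan's own figure.** No standard deviation is given, so 26 per group cannot be reproduced. Solving for it with the t distribution gives an implied SD of about 1.51 if 26 is the number analysed. That fixes the standardised effect used in step 1.

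**1. Arm sizes.** The number in one arm is Binomial(52, 0.5).

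- P(26:26) = 0.110, so one arm is below 26 with probability 1 − 0.110 = 0.890.
- P(22:30 or worse) = 0.332; P(20:32 or worse) = 0.126.
- Relative efficiency of 22:30 is 4 × 22 × 30 / 52² = 0.976.
- Power is 80.0% at 26:26, 79.8% at 28:24, 79.1% at 30:22 and 77.8% at 32:20. Averaged over all splits it is 79.2%, a loss of 0.8 points.
- For comparison, 20% drop-out leaves 26 × 0.8 = 20.8 per arm and power of about 70% at the same effect.

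Arm size is therefore a minor matter.

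**2. Stream mix.** Let X ~ Binomial(m, 0.5) be the women of the smaller stream in arm 1, and Y ~ Binomial(52 − m, 0.5) the others in arm 1. The gap in stream share is D = |X/(X+Y) − (m−X)/(52−X−Y)|. Summing the exact probabilities over all (X, Y), and applying a two-sided Fisher test at 0.05 to each table, gives:

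| m | P(D ≥ 15 points) | P(D ≥ 20 points) | Share of gaps ≥ 15 points flagged by Fisher |
|---|---|---|---|
| 5 | 0.070 | 0.012 | 0.187 |
| 8 | 0.150 | 0.047 | 0.181 |
| 10 | 0.193 | 0.079 | 0.155 |
| 13 | 0.234 | 0.095 | 0.111 |
| 16 | 0.259 | 0.135 | 0.134 |
| 20 | 0.283 | 0.156 | 0.161 |
| 26 | 0.332 | 0.134 | 0.075 |

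**3. The safeguard.** The last column implies that about 81–93% of gaps of 15 points or more pass unflagged. One example: 16 social-media women split 11:5 in arms of 26 give 11/26 − 5/26 = 42.3% − 19.2% = 23.1 points, with Fisher p = 0.13. Stream would not enter the model.

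The article does not say which baseline test would be used. Applying an uncorrected chi-squared test to the same tables flags 14–36% of these gaps for m = 8 to 26, still a minority. At m = 5 it flags 73%, but its approximation is poor with so few women.

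**The case against.** Much of the opposing case stands.

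- **Chance imbalance is not bias.** Simple randomisation is valid, and its variability is reflected in the p-values and intervals. A reader might infer that the T2 effect is confounded beyond recovery. The article does not support that: stream is known for every woman and can be modelled, and treatment data are to be taken from records. The records are not a full substitute for stream, however. The stated purpose refers to the intervention period, and treatment received after randomisation may itself be affected by allocation, whereas stream is fixed beforehand.
- **The 89% figure invites too strong a reading.** A reader might infer that simple randomisation is what defeats "A minimum of 26 patients in each group at each time point". It is not: a perfect 26:26 split with the assumed 20% drop-out still leaves about 21 per arm. The shortfall is mainly a drop-out matter, and unequal arms add little to it.
- **The link from stream to treatment is inferred.** The article does not say that social-media women are off waiting lists or receive less care by T2.
- **The shift may be small.** With assumed values of a 20-point stream gap, a 50-point difference in treatment uptake and a 2-unit treatment effect, the T2 contrast moves by 0.2 × 0.5 × 2 = 0.2 units, against a target of 1.2.
- **The allocation remedy may be late.** Recruitment has run since 2016 and was to finish in 2020. The settings of the web-generated list are not described either. If it fixed equal totals, the arm-size result would fall away and the label would be wrong, but the stream point would remain.

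What survives is narrow: a plausible prognostic variable is left to chance at allocation, and then to a test that would rarely pick it up.

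**Conclusion.** The point holds in a limited form. A stream gap of 15 points or more arises in about 7–33% of trials and one of 20 points or more in about 1–16%, and the stated adjustment rule would miss most gaps of 15 points or more. The harm is loss of precision and interpretability at T2 in a small trial.

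This rests on three assumptions: the smaller stream has 5 to 26 of 52 women, Fisher's test is the baseline test, and stream is related to treatment received by 9 months. If the last is false, the gaps are harmless. The finding does not show that the trial is biased or that its power is materially reduced by the allocation method.

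**What to change.** **Analysis, for all women.** In the Statistical analysis plan section, name recruitment stream (waiting list or social media) as a prespecified fixed factor in the mixed model and in the general linear models, whatever its baseline difference. This replaces the significance-triggered rule for this variable. Because the concern is about T2, let the stream effect differ by visit in the mixed model. Report the split by arm and stream.

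**Allocation, for any women still to be randomised.** Use a concealed computer-generated list in randomly varying permuted blocks, stratified by stream, with block sizes unknown to those who screen. As an illustration, stratified blocks of 4 applied to all 52 women (streams of 10 to 26) keep each arm between 24 and 28 and the stream gap at about 8 points or less.

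**Cost.** One degree of freedom in each general linear model, and two more in the mixed model for stream by visit (three time points). A new list is needed only if recruitment is still open, and allocation becomes slightly more predictable in an open trial, which varying block sizes limit.

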### Intervention

2.5

The treatment is provided via an internet-based secure platform with dual authentication that is approved for regular health care use and was developed by psychologists from the Pain Treatment Centre and the Department of Ear, Nose and Throat Diseases at Uppsala University Hospital in Sweden. The platform contains material such as videos, audio files, and self-assessment questionnaires. The platform enables the communication between participants and eCoaches, who are research assistants trained to provide written feedback on participants' assignments after module completion and to respond to their questions. Standard answers are used as templates to address questions and to provide feedback. If the eCoach has concerns about how to conduct treatment or write feedback, they discuss with a senior researcher. A national personal identification number and a password are necessary to securely access the platform. All communication concerning the treatment is handled within the platform. The participants can contact the eCoaches and receive a response within 3 working days. The eCoaches monitor treatment and notify the participants via reminder emails if they have been inactive for more than 4 days.

The treatment consisted of six different modules, spanning a 6-week treatment period, based on an ACT manual for the treatment of patients with chronic pain (Buhrman et al., 2013), and adapted for patients with vulvodynia by a multidisciplinary team (gynaecologist, psychologist physiotherapist and midwife) with experience in treating patients with vulvodynia. The treatment was CBT-based, with ACT components, with a multidiscplinary approach; the CBT/ACT components were used as a framework during the entire treatment, for example, the modules 3 and 4 had information and exercises about valued direction and management of negative thoughts (Table 1). The modules are divided into information and treatment assignments (Figs. 1 and 2). The information modules contain knowledge about anatomy, pelvic floor muscle function, sexuality, chronic pain, and vulvodynia. Some parts of patient education are also given in video format, such as information regarding pelvic floor anatomy instruction, pelvic floor exercises is given by a physiotherapist, and information about vulvodynia, communication with partner, and sexuality is given by a midwife. The exercise modules contain exercises related to CBT-based ACT. Further, daily exercises were recommended and consisted of mindfulness, pelvic floor muscle exercises, and desensitisation exercises. The participants in the control group, on request, are given access to the internet-based treatment after 10.5 months from study inclusion. The average number of words per module is 7401 (module 1: 8143, module 2: 8760, module 3: 7638, module 4: 6755, module 5: 8813, and module 6: 4294). It is estimated that about 30 min per day are needed to complete one module per week. Written feedback, consisting of positive reinforcement related to a participant's assignment, is provided weekly to the participants on their submitted assignments after module completion by the eCoaches.

**Table 1 t0005:** Description of the six different modules included in the intervention group.

Module	Information	Exercises	Daily training
1. Introduction	Vulvodynia Chronic pain Primary and secondary suffering CBT, ACT and internet-based treatment	Primary and secondary pain Circle of pain Expectations and planning Personal commitments	Mindfulness exercise
2. Pelvic floor	Anatomy of the vulva Pelvic floor Stress and anxiety Exposure	Things I have done Willingness diary	Mindfulness exercise Pelvic floor exercise Exposure exercise
3. Values	Valued direction Willingness	What do you want your life to stand for? Life compass Why willingness? To have hope	Mindfulness exercise Pelvic floor exercise Exposure exercise
4. Thoughts	Negative thoughts Alternative attitude Sexuality	To have and to be a thought The little word”and” Reformulate goals	Mindfulness exercise Pelvic floor exercise Exposure exercise
5. Relations	Relations Sexual identity Desire Communication Exposure	Body contact Stoplight	Mindfulness exercise Pelvic floor exercise Exposure exercise
6. Maintenance	Summary of the sections The new contract Maintenance Closure	Reflections Evaluate my commitments Maintenance plan	Mindfulness exercise Pelvic floor exercise Exposure exercise

